## Abstract

**Background:**

Patients in hospitals and nursing homes are at risk of the development of, often preventable, adverse events (AEs), which threaten patient safety. Guidelines for prevention of many types of AEs are available, however, compliance with these guidelines appears to be lacking. Besides general barriers that inhibit implementation, this non-compliance is associated with the large number of guidelines competing for attention. As implementation of a guideline is time-consuming, it is difficult for organisations to implement all available guidelines. Another problem is lack of feedback about performance using quality indicators of guideline based care and lack of a recognisable, unambiguous system for implementation. A program that allows organisations to implement multiple guidelines simultaneously may facilitate guideline use and thus improve patient safety.

The aim of this study is to develop and test such an integral patient safety program that addresses several AEs simultaneously in hospitals and nursing homes. This paper reports the design of this study.

**Methods and design:**

The patient safety program addresses three AEs: pressure ulcers, falls and urinary tract infections. It consists of bundles and outcome and process indicators based on the existing evidence based guidelines. In addition it includes a multifaceted tailored implementation strategy: education, patient involvement, and a computerized registration and feedback system. The patient safety program was tested in a cluster randomised trial on ten hospital wards and ten nursing home wards. The baseline period was three months followed by the implementation of the patient safety program for fourteen months. Subsequently the follow-up period was nine months. Primary outcome measure was the incidence of AEs on every ward. Secondary outcome measures were the utilization of preventive interventions and the knowledge of nurses regarding the three topics. Randomisation took place on ward level. The results will be analysed separately for hospitals and nursing homes.

**Discussion:**

Major challenges were the development of the patient safety program including a digital registration and feedback system and the implementation of the patient safety program.

**Trial registration:**

Trial registration: ClinicalTrials.gov ID [NCT00365430]

## Background

Over the past seventeen years several studies showed that patients are at risk of injuries or even death as a result of care delivered in hospitals [1-11]. These studies show that 2.9 to 16.6% of patients in acute care hospitals experienced at least one adverse event (AE) (Table 1) [1,2,9-11]. In 5 to 13% of these events the patients died [1-3,7,9-11]. Half of all events are considered preventable [1,3,6,9-11]. While these studies did not include nursing homes, other studies show that AEs, such as urinary tract infection, pneumonia, falls, pressure ulcers and medication errors, also occur frequently in nursing homes [12-14]. These events can often be linked directly to suboptimal nursing care, and they are generally considered preventable.

**Table 1 T1:** Definitions

**Adverse event**
An adverse event (AE) is defined as an unintended injury that results in prolonged stay, disability at the time of discharge, or death and is caused by health care management rather than by the patient's underlying disease process [1,3,9,11].
**Bundle**
A bundle is a structured way of improving the processes of care and patient outcomes: a small, straightforward set of practices – generally three to five – that, when performed collectively and reliably, have been proven to improve patient outcomes [17].

Many guidelines for the improvement of nursing care are available, however compliance with these guidelines appears to be lacking [15]. Generally, many factors or barriers may influence compliance -or noncompliance- with a guideline. These general barriers may be related to the individual (e.g. knowledge, skills, attitudes, motivation) or the individual's social context (e.g. patients, colleagues, culture), and the organisational setting (e.g. financial, equipment). Moreover, the large number of guidelines competing for attention makes it difficult to keep track of all of them. In addition organisations must translate each guideline to their own target group, and develop and organise their own information and education, which is a time-consuming process. Also, there is a lack of insight into actual performance of guideline based care, e.g. by using quality indicators [16]. As a result it is difficult to implement all available guidelines necessary for good quality daily nursing care. This situation is at odds with the responsibility of professionals to ensure patient safety. A program that allows organisations to implement multiple guidelines simultaneously may facilitate guideline use and thus improve patient safety.

The aim of this study is to develop and test such an integral patient safety program that addresses several AEs simultaneously in hospitals and nursing homes.

In this paper we will report on the design of this study, which has two phases. The first phase concerns the development of the patient safety program for three frequently occurring nursing care related AEs: pressure ulcers, falls and urinary tract infections. The second phase describes the evaluation of the patient safety program in a cluster randomised trial.

## Methods and design

### Phase 1: the development of the patient safety program

#### General focus of the program

From September 2005 – July 2006 we developed the integral patient safety program (SAFE or SORRY?) for the prevention of pressure ulcers, falls and urinary tract infections in hospitals and nursing homes. The program consists of bundles [17] (Table 1) and outcome and process indicators based on evidence based guidelines for pressure ulcers, falls and urinary tract infections.

For the implementation of guidelines, multifaceted implementation strategies are probably more effective than single strategies, as multifaceted strategies address multiple barriers to guideline adherence [16]. Therefore, we aimed at developing a multifaceted strategy for the implementation of these bundles.

#### Development

We developed the patient safety program with experts on each topic by collecting the existing guidelines [18-26] and supplementary material [27-40]. Based on this information the research group and the experts achieved consensus about the essence of the guidelines and formulated the bundles and indicators (Table 2). They developed a multifaceted implementation strategy consisting of education, patient involvement, feedback through a computerized registration program and an implementation plan for every ward (Table 3).

**Table 2 T2:** Process (P) and outcome (O) indicators

**Pressure Ulcers**
% patients where nurses assessed pressure ulcer risk (P)
% patients at risk for pressure ulcers (O)
% patients with pressure ulcers grade 2 or worse (O; prevalence)
% patients developing nonblanchable erythema (O; incidence)
% patients developing pressure ulcers grade 2 or worse (O; incidence)
% patients developing pressure ulcers grade 2 or worse at the heels (O; incidence)
% at risk patients receiving permanent adequate preventive measures (P)
% patients developing pressure ulcers despite the preventive measures (O)
% patients with pressure ulcers increasing in grade and/or becoming more serious (O)
**Urinary tract infection**
% patients where nurses assessed risk for urinary tract infection (P)
% patients at risk for urinary tract infections (O)
% patients with urinary tract infections (O; prevalence)
% patients with fecal incontinence with urinary tract infections (O; prevalence)
% patients with urinary tract infections who have of had a bladder catheter (O; prevalence)
% patients developing urinary tract infections (O; incidence)
% at risk patients receiving permanent adequate preventive measures (P)
% patients with an appropriate/correct indication for indwelling bladder catheter (P)

**Falls**
% patients where nurses assessed risk for falling (P)
% patients at risk for falls (O)
% patient falls (O; prevalence)
% patients at risk that received multi-factorial measures (P)
% patients in which both risk factors and multi-factorial measures were evaluated regularly (P)
% patient that fell despite multi-factorial measures (O)

**Table 3 T3:** Operational implementation strategies

**Education**
Group lesson on the wards for all nurses
A CDrom with education material and a knowledge test
Case discussions on every ward
**Patient involvement**
An information folders for the prevention of pressure ulcers, urinary tract infection and falls, separately. In addition to giving oral information nurses were asked to give the folder to patients at risk for the specific AE.

**Feedback**
The nurses register the patient's daily care and the presence or absence of an AE in a computerized registration system. This digital program generates feedback by charts on the process and outcome indicators.

#### Tailoring

We discussed the bundles and indicators with the user group. This group consisted of two researchers (LS and [name]), seventeen future users of the patient safety program, two medical doctors and an implementation expert ([name]) and met five times. During the first meeting everyone was informed about the aim and work methods. During the next three meetings the group was split up into two smaller groups: a group with users from the hospitals and a group with users from the nursing homes. In each group we had focus discussions about the use of the bundles and indicators and the expected barriers for implementation. During the fifth meeting the group tested the computerized registration program. With this information, and the outcome on the knowledge test from the baseline measurement (phase 2), we tailored the education for the nurses to each individual ward in the intervention group. In a last meeting, the users of the intervention group tested the final educational material and the patient information. In order not to contaminate the control group with the elaborated education material and patient information, the users of this group were not invited to this last meeting.

Table 3 describes the concrete implementation strategies for the patient safety program. In addition, every intervention ward appointed two key nurses to the study. Together with the head nurse they were responsible for the implementation of the patient safety program on their ward. At the start of the implementation period these key nurses received a training in the use of the patient safety program. We also discussed the results of the baseline measurements (phase 2) and the educational material, and all educational activities on the wards were planned and organised. The key nurses and the researcher had periodical contact about the progress on the ward, throughout the implementation period.

### Phase 2: cluster randomised clinical trial to evaluate the patient safety program

#### Study design and setting

A cluster randomised trial was conducted between September 2006 and November 2008 in the Netherlands. Hospitals and nursing homes were asked to participate with two or four, more or less comparable, wards. The hospital wards (n = 10) were internal medicine wards (n = 4) and surgical wards (n = 6) from four hospitals. The nursing home wards (n = 10) were wards with patients with physical impairments (no dementia)(n = 7) or rehabilitation wards (n = 3) from six nursing homes. The randomisation of the wards was stratified for centre and type of ward (Figure 1) and took place prior to baseline data collection.

**Figure 1 F1:**
[figure not shown]
**Randomisation**.

Baseline data collection took place from September through November 2006. Subsequently, the patient safety program was implemented on the intervention wards: five hospital wards and five nursing home wards from December 2006 – February 2008. The wards of the control group continued care as usual. The follow-up period was nine months and continued until the end of November 2008.

The Medical Ethics Committee of district Arnhem – Nijmegen assessed the study and waived the need for complete evaluation of the study.

#### Study population

Adult patients (≥ 18 years) admitted to the hospitals or the nursing homes during our study, were asked to participate. Hospital patients with an expected stay of at least five days were asked within 48 hours after admission. After a written informed consent the research assistants visited the patients once a week. All patients with at least a second visit were included in this study.

All (clinical) nurses at the wards participated in our study. Nurses' aids and students were excluded.

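### Hospital patients enter on a forecast stay and individual consent after their ward's arm is fixed, so the risk mix of enrolled patients can differ by arm, and the planned covariates cannot correct it

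*Protocol article*

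**What the plan says.** All references are to the protocol article.

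- **Allocation** (Study design and setting). Wards were randomised, stratified by centre and type of ward, and this "took place prior to baseline data collection".
- **Program** (same section, below Figure 1). After baseline (September to November 2006), "the patient safety program was implemented on the intervention wards: five hospital wards and five nursing home wards", from December 2006 to February 2008. Nine months of follow-up came next.
- **Openness** (Tailoring). The article says "every intervention ward appointed two key nurses to the study". Of the control-ward users it says that "the users of this group were not invited to this last meeting".
- **Hospital entry** (Study population). The invitation rule reads "Hospital patients with an expected stay of at least five days were asked within 48 hours after admission". Consent is individual and in writing, and the weekly visits by research assistants start only once it is given. A further condition then decides who counts: "All patients with at least a second visit were included in this study".
- **Patient information** (Table 3). "In addition to giving oral information nurses were asked to give the folder to patients at risk for the specific AE".
- **Analysis** (Statistics). The arms are compared on AE incidence in follow-up by random effects Poisson regression. The covariates are ward as a random effect, institution and the ward's baseline results. No patient-level risk factor is named.
- **Risk measurement** (Outcome measures). Hospital patients are assessed with the PrePURSE for pressure ulcers, the STRATIFY for falls, and four listed risk factors for urinary tract infection (UTI).

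**The concern.** Randomising wards balances wards in expectation. It does not by itself balance the patients who later join the study on those wards. Two entry steps come after allocation: a judgement within 48 hours about expected stay, and the patient's own decision to consent. On intervention wards the program is evident to ward staff by follow-up, so either step could work differently there.

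The primary comparison uses patients enrolled in follow-up. If high-risk patients make up a different share of those enrolled in one arm, AE incidence differs between arms even if the program does nothing. Under-enrolment of high-risk patients on intervention wards would imitate benefit; over-enrolment would hide it. The ward's baseline results handle stable ward differences, but those patients were enrolled before the program started, so the covariate holds no information on a shift in enrolment that the program brings about.

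**Working it through.** **Step 1: reproduce the plan's figure.** Inputs from Statistics: 12% versus 6%, two-sided alpha 0.05, 80% power, intraclass correlation 0.01, 1250 hospital patients per group. Study design gives five hospital wards per arm.

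- Individually randomised size, pooled two-proportion formula without continuity correction: 356 per arm.
- Patients per ward: 1250/5 = 250. Design effect: 1 + (250 − 1) × 0.01 = 3.49.
- Required: 356 × 3.49 = 1242 per arm. Letting ward size follow the total, 356 × 0.99/(1 − 356 × 0.01/5) = 1224.

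Both are within 3% of 1250, and power at 1250 is 80.2%. The stated size reproduces. The effective size per arm is 1250/3.49 = 358.

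**Step 2: assumptions.** The article gives no enrolment rates, so these are mine: no true program effect; 30% of eligible patients high-risk; overall risk 12%; high-risk patients at R times the risk of the others, with R = 2 or 4. On intervention wards high-risk patients are enrolled at k times the relative rate of the others; on control wards k = 1.

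**Step 3: formulas.**

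- Low risk = 0.12/(0.3R + 0.7); high risk = R × low risk. R = 2 gives 9.2% and 18.5%. R = 4 gives 6.3% and 25.3%.
- High-risk share among those enrolled on intervention wards: s = 0.3k/(0.3k + 0.7).
- Apparent intervention risk: r = s × high risk + (1 − s) × low risk.
- Rejection probability: two-sided 5% normal test with 358 per arm and standard error √[(0.12 × 0.88 + r(1 − r))/358].

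Example, R = 4 and k = 0.7: s = 0.21/0.91 = 23.1%; r = 0.231 × 25.3% + 0.769 × 6.3% = 10.7%; risk ratio 0.107/0.12 = 0.89; standard error 0.0237; shift 0.0131/0.0237 = 0.55 standard errors; rejection 8.6%.

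**Step 4: results with no true effect.**

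| R | Under-enrolment | Apparent risk | Risk ratio | Share of 6-point target | Two-sided error |
|---|---|---|---|---|---|
| 2 | 10% | 11.8% | 0.98 | 3% | 5.1% |
| 2 | 20% | 11.6% | 0.97 | 7% | 5.3% |
| 2 | 30% | 11.4% | 0.95 | 11% | 5.8% |
| 2 | 50% | 10.9% | 0.91 | 19% | 7.7% |
| 4 | 10% | 11.6% | 0.97 | 7% | 5.3% |
| 4 | 20% | 11.2% | 0.93 | 14% | 6.4% |
| 4 | 30% | 10.7% | 0.89 | 22% | 8.6% |
| 4 | 50% | 9.7% | 0.80 | 39% | 17.2% |

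**Step 5: opposite direction.** With R = 4 and k = 1.5, s = 0.45/1.15 = 39.1% and the apparent intervention risk under no effect is 13.7%, a bias of 1.7 points against the program. If the program truly halves risk, the observed intervention risk is 6.9% and power falls from about 80% to about 65%.

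**The case against.** The case on the other side is substantial, and much of it stands.

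- **Who recruits is not stated.** A reader might infer that recruiters knew each patient's arm with certainty. The article does not say who forecasts the stay or who invites; the only study role named under Study population is the research assistant. Consecutive or blinded screening may be described in a full protocol that is not shown. What the documents support is narrower: the arm was fixed, and on intervention wards it was evident to ward staff.
- **The folder route is conjecture.** A reader might infer that the oral information and folder change consent among at-risk patients. Nothing in the article places the folder before consent, links it to willingness to join, or says how it was handed out during follow-up.
- **Over-forecasting is blunted.** Patients wrongly expected to stay long mostly lack a second visit and drop out. Missed long stayers remain, and no passage suggests that the program alters forecasts.
- **A large bias needs extreme inputs.** An error near 17% requires both a fourfold risk contrast and half-rate enrolment of high-risk patients in one arm only.
- **Recruitment is described as past.** Rewriting eligibility or re-timing the folder is therefore not a cheap change.

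It is also said that this is a generic limit of open cluster trials with individual consent. That is true, but it does not answer the point about the analysis: the named covariates leave the gap open, while patient-level risk measures are already part of the study.

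**Conclusion.** The concern holds as a risk, not as a demonstrated bias. Hospital patients join by a forecast and by individual consent after allocation, the program is evident on intervention wards by follow-up, and the planned covariates cannot absorb a later change in who enrols. The direction is unknown. For 10% to 30% under-enrolment and a twofold to fourfold risk contrast, the spurious risk ratio is 0.98 to 0.89 and the two-sided error 5.1% to 8.6% instead of 5%. That is modest beside the planned halving, but it would matter if the observed effect were small. These sizes rest on the assumed 30% high-risk share, risk contrasts and enrolment ratios, and on a two-proportion approximation to the Poisson model. Individual consent also applies in nursing homes; the forecast criterion is limited to hospitals, and only hospitals were quantified.

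**What to change.** 1. Keep the Poisson random-effects model as primary. Beside it, pre-specify an analysis that adds patient-level risk at the first visit: PrePURSE, STRATIFY, a UTI in the last two years, and other UTI risk factors that the program cannot have changed by then. Run it regardless of any test of imbalance.
2. Leave out items the program can alter before the first visit, above all a catheter in situ. Avoiding unnecessary indwelling catheters is one of the program's own preventive targets, so adjusting for catheter use could remove real benefit.
3. Where hospital admission lists allow, report eligible, invited and consented patients, and first-visit risk, by arm and period.
4. Only if recruitment is still open, replace the individual forecast with an objective rule based on admission facts, applied identically on all wards.

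The cost is one further analysis and one table, from data that the study already collects or that hospitals may hold. The article does not state at which visit the risk scores were taken, so this must be confirmed. The downside is slight over-adjustment if the program had already changed a recorded risk item by the first visit. For that reason the adjusted analysis should accompany the primary one and not replace it.

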#### Outcome measures

The primary outcome measure was the incidence of AEs (sum of the incidence of pressure ulcers, urinary tract infections and falls).

A *pressure ulcer *is an area of localised damage to the skin and underlying tissue caused by a combination of pressure and shear[21]. Pressure ulcers are classified in four grades according to the guidelines [19,21,40]. Pressure ulcers were considered present if a patient developed a PU grade 2 or worse. If a patient had a PU grade two or worse at the first visit, that PU lesion was excluded from the registration of PUs until the PU healed. Patients with an already present PU grade two or worse were only registered if they developed additional PU lesions.

A *urinary tract infection *is bacteriuria with clinical symptoms as: frequent urinating, pain while urinating, abdominal pain, fever and delirium, urinary incontinence [18,24]. During this study we defined a urinary tract infection as present if it was diagnosed by a medical doctor. Patients were excluded from the registration of urinary tract infection for a period of three weeks if they had a urinary tract infection until the infection was cured.

A *fall *is an unexpected event in which the participant comes to rest on the ground, floor, or lower level [20,41]. In this study the falls were measured by examining the patient files, assuming that if a patient fell it was reported in his or her file.

The secondary outcome measures were 1) the percentage of patients that received preventive care and 2) the knowledge of nurses regarding the three topics.

*Prevention *is important in patients at risk for one of the AEs. Preventive measurements were considered present when the care was performed according to the guideline.

The risk of *pressure ulcers *was measured with the PrePURSE [27] and the Braden scale [42] in hospitals and nursing homes, respectively. Next preventive care was measured: position while lying or sitting; if patients' heels were lifted; use of pressure-reducing material or alternating pressure material in bed or chair; presence of a repositioning scheme.

Hospital patients were at risk for a *urinary tract infection *if they had at least one of the next four risk factors [18,23]: 1) a urinary catheter in situ or the week before, 2) incontinence of faeces, 3) urinary retention or 4) a urinary tract infection in the last two years. According to the guideline, all nursing home patients were considered at risk for a urinary tract infection [18]. Next preventive care was measured: personal hygiene, frequent toilet visits, unnecessary indwelling catheter and unobstructed urine flow.

To identify hospital patients at risk for *falls *we used the STRATIFY [43]. According to the guideline all nursing home patients were considered at risk for falls, except those who were totally immobile [20]. Next preventive care was measured: if the file had a written multidisciplinary plan with multi-factorial preventive interventions; a periodic evaluation of the multidisciplinary plan; a periodic evaluation of the multi-factorial risk factors for falls.

The *knowledge *of nurses about risk assessment and effective preventive care was measured using a written knowledge test. Each topic had twenty questions, on which nurses could answer 'correct', 'not correct', or 'do not know'.

The knowledge test was developed from questionnaires [44] (knowledge test used in an implementation study of a pressure ulcer guideline in the Netherlands ([name] 2004) and geriatric educational material of the prevention of falls, 2007) and student tests of the HAN University of Applied Sciences on the three topics. The face validity was tested by sending the questionnaire to the members of the research group (LS, [name], [name] and [name]), and the expert on each topic. Finally, nurses in hospitals and nursing homes were asked to pretest the questionnaire.

